## Abstract

**Background:**

This multicenter, three-armed, parallel, single-blind randomized controlled trial (RCT) primarily aims to compare the efficacy of virtual reality exposure therapy (VRET) with that of acceptance and commitment therapy (ACT) and treatment as usual (TAU) to depreciate the degree of alcohol craving among alcohol use disorder patients who have undergone in-patient detoxification across four timelines (t_0_ = baseline prior to intervention, t_1_ = 4 weeks after baseline, t_2_ = 12 weeks after baseline, and t_3_ = 24 weeks after baseline). The secondary aims of this RCT are to compare the efficacy of VRET with that of ACT and TAU to alleviate the severity of alcohol use disorder, dissipate comorbid depressive and anxiety symptoms, and normalize event-related potential (ERP) in electroencephalogram (EEG) monitoring across the four timelines.

**Methods:**

Initially, after 2 weeks of in-patient detoxification, 120 patients with alcohol use disorder will be randomized into three groups (VRET, ACT, and TAU control groups) via stratified permuted block randomization in a 1:1:1 ratio. Baseline assessment (t_0_) commences, whereby all the participants will be administered with sociodemographic, clinical, and alcohol use characteristics questionnaire, such as Alcohol Use Disorder Identification Test (AUDIT), Penn Alcohol Craving Scale (PACS), Hamilton Anxiety Rating Scale (HAM-A), and Hamilton Depression Rating Scale (HAM-D), while event-related potential (ERP) detection in electroencephalogram (EEG) will also be carried out. Then, 4 weeks of VRET, ACT, and non-therapeutic supportive activities will be conducted in the three respective groups. For the subsequent three assessment timelines (t_1_, t_2_, and t_3_), the alcohol use characteristic questionnaire, such as AUDIT, PACS, HAM-D, HAM-A, and ERP monitoring, will be re-administered to all participants.

**Discussion:**

As data on the effects of non-pharmacological interventions, such as VRET and ACT, on the treatment of alcohol craving and preventing relapse in alcohol use disorder are lacking, this RCT fills the research gap by providing these important data to treating clinicians. If proven efficacious, the efficacy of VRET and ACT for the treatment of other substance use disorders should also be investigated in future.

**Clinical trial registration:**

NCT05841823 (ClinicalTrials.gov).

## 1. Introduction

Alcohol is an easily accessible substance that is associated with the risk of various morbidity and mortality. Alcohol consumption per capita in the world rose from 5.5 L in 2005 to 6.4 L in 2010, and it remained at 6.4 L in 2016. As alcohol consumption has not depreciated, in 2016, alcohol-related disability-adjusted life years (DALYs) stood at 132 million and mortality was at 3.0 million deaths worldwide. Hence, alcohol contributed to 5.0% of DALYs and 5.3% of all-cause mortality worldwide (1).

Similarly in China, alcohol use is on the rise, in which the prevalence of alcohol consumption among those aged 18 years and older rose from 35.7% in 2007 to 37.1% in 2013 and 41.3% in 2015, according to the China Chronic Disease and Nutrition Surveillance (CCDNS). Unfortunately, the alcohol-related burden of disease and injury increased rapidly in China from 1990 to 2017, in which the prevalence of DALYs and age-standardized DALY rate was at 58.51 and 16.02%, according to the Global Burden of Disease study. In 2013, China registered 381,200 alcohol-related mortality cases and alcohol caused reduced life expectancy of the Chinese people by 0.43 years (2).

In Malaysia, the National Health and Morbidity Survey (NHMS) 2011 revealed that the prevalence of current alcohol use was 11.6%, and among the alcohol users, 23.6% of them practiced hazardous drinking. Among the ethnicity, Malaysian Chinese is more prevalent to consume alcohol (3). The NHMS 2019 in Malaysia reported a similar prevalence of alcohol consumption in the country at 11.5%, and Malaysian Chinese remained as the most prevalent ethnicity to consume alcohol (4).

### 1.1. Alcohol use disorder and the major issue contributed by alcohol craving

One of the commonest negative impacts of alcohol consumption is the occurrence of alcohol use disorder. Alcohol use disorder is a chronic and recurrent mental disorder (5). It will affect the brain's ability to control emotions, decisions, and behaviors, resulting in the decline of work and learning abilities, impaired physical and mental health, and even legal problems (5). Alcohol use disorder poses a serious threat to individual health, family wellbeing, and social stability (6). Therefore, how to effectively treat the disease and prevent relapse is of great significance.

The core symptoms of alcohol use disorder include two aspects: physical dependence based on increased alcohol tolerance and withdrawal reaction and psychological dependence based on alcohol craving (5, 6). Currently, the clinical treatment for alcohol use disorder is focused on reducing physical dependence, and in fact, this is the only effective treatment available for alcohol use disorder. Treatment methods for physical dependence mainly include the prescription of benzodiazepines which is administered to alleviate withdrawal symptoms, low-dose antipsychotic to relieve psychotic symptoms associated with alcohol withdrawal, and adequate vitamin B6 supplementation to prevent Wernicke encephalopathy. However, most patients remain psychologically dependent on alcohol during abstinence, and their hazardous drinking persists due to the satisfaction and euphoria contributed by persistent drinking, resulting from strong alcohol craving (7), even after receiving standardized in-patient treatment. This psychological dependence on alcohol is hard to resist, so it is extremely difficult to maintain long-term abstinence, and hence, alcohol use disorder is prone to relapse (5). Since psychological dependence is the key factor leading to relapse of hazardous alcohol use after abstinence, it is essential to monitor and manage alcohol craving to improve the therapeutic outcome of alcohol use disorder.

### 1.2. Exploration of electrophysiological monitoring technology based on electroencephalogram (EEG) in alcohol use disorder

In recent years, the application of electrophysiological technology to explore the mechanism of addiction diseases has become an important research interest. Electrophysiological monitoring methods based on EEG have made a lot of progress in the diagnosis and treatment of alcohol use disorder, including resting EEG and task-state EEG, and the latter is mainly event-related potentials (ERP) and event-related oscillations (ERO) (6). EEG-based monitoring technology can reflect neuropsychological factors from different perspectives, quantify brain energy fluctuations under specific mental activities to a certain extent (8), and help judge the severity of alcohol use disorder.

ERP is an objective detection tool to study psychological activities, which can reflect the cognitive process through the EEG activities under task state (8, 9). ERP has very high temporal resolution, which can reflect the dynamic balance between excitation and inhibition of brain neural network within milliseconds (9), so it is suitable for studying rapidly changing mental activities. Moreover, the detection equipment is convenient and can overcome small movement or noise, which is widely applied to various subjects. A previous study suggested that the abnormal amplitude of ERP might be a disease marker of substance dependence or a potential neurobiological endophenotype of addiction (10). Another study showed that alcohol users had enhanced ERP response to alcohol-related cues, especially in male patients (11). A previous study by our team found that there were positive results in EEG analysis of alcohol-dependent patients in craving state evoked by static pictures with alcohol cues (12). However, the alcohol-dependent group showed lower N200 amplitude and higher P300 amplitude under the stimulation of alcohol cues and was positively correlated with the scores of subjective craving scales. Alcohol cue reactivity was used to evoke alcohol craving in patients with alcohol use disorder, and this ERP was monitored at the same time. In this way, it was possible to objectively assess the psychological activities associated with alcohol craving.

### 1.3. Application of virtual reality technology in alcohol addiction

Virtual reality (VR) is a computer simulation technology, which synthesizes various computer functions to generate a realistic virtual environment (VE). In the digital world created by VR-related devices, users can get an “immersive” experience across time and space constraints, and the VE with multimodal stimuli can be customized and changed according to user needs (13). In recent years, VR technology has been increasingly applied in the medical field and has been well-developed in psychological rehabilitation, especially in the treatment of anxiety disorder and post-traumatic stress disorder (14). VR therapy, as an intervention method with flexible treatment time, low cost, and personalized scheme, should be applicable to the treatment of a variety of mental diseases. At present, the application of VR technology in alcohol use disorder is still in the early stage of development and implementation.

Some pieces of research try to integrate VR into the psychotherapy of alcohol use disorder and have obtained new discoveries and understandings. Cue exposure therapy (CET) aims to reduce cue reactivity through repeated exposure to substance-related cues, leading to habituation, so as to reduce alcohol craving (15). However, a meta-analysis pointed out that the efficacy of traditional CET in the treatment of alcohol use disorder was limited or even not better than CBT (16), which may be associated with the failure to fully simulate the real exposure environment in many CET cases. In view of this situation, researchers have tried virtual reality exposure therapy (VRET). VR technology can simulate realistic exposure situations to improve the factors that limit CET efficacy. VRET provides some immersive three-dimensional environments and social interactions similar to the real world, and it treats diseases in a novel and attractive way (17). Bordnick et al. (18) found that alcohol cues VE evoked higher subjective craving in alcoholics than neutral cues VE, and patients paid more attention to the alcohol cues. In addition, subjects reported a good sense of presence (18). Cho et al. pointed out that the situation with social pressure provided by virtual characteristics can evoke a higher degree of alcohol craving than the situation without social pressure, and they believed that the social pressure provided by VR was more important than mere alcohol cues (19). There is reason to believe that the more complex, real-life cue exposure scenario provided by VR is conducive to sufficiently evoking craving, so as to implement better VRET.

### 1.4. Application of acceptance and commitment therapy in addiction medicine

ACT is a third-generation cognitive behavioral approach that uses acceptance and mindfulness processes, as well as commitment and behavior change processes to produce psychological flexibility (20). ACT was designed to increase adaptive coping through acceptance, cognitive defusion, mindfulness, and perspective-taking exercises while supporting clients in aligning behavior with their personal values (21). The objectives of the therapy are for clients to learn that avoidance, suppression, or attempts to control difficult thoughts can be counterproductive. Clients also learn to focus on behaviors and actions that are in line with their individual values (22, 23).

A meta-analysis reported that ACT showed better efficacy compared with other therapies when applied to substance use disorders (SUDs), including tobacco, alcohol, and illicit drug use (24). A study comparing the efficacy of ACT and cognitive behavioral therapy (CBT) in treating SUD found that ACT was better than CBT in reducing drug use and improving mental health (25). Therefore, in the long term, ACT may be more appropriate than CBT for treating substance addiction. Another study on male smokers showed that ACT significantly improved smoking cessation rate and alleviated comorbid depression and anxiety symptoms (26). With the promising potential of ACT in the treatment of emotional disorders and SUD, we are interested in whether ACT can more specifically be used for treating alcohol use disorder. A systematic review suggested that ACT provides an alternative to existing treatments for alcohol use disorder, with promising results, but further research is needed (27). Witkiewitz et al. (28) pointed out that alcohol addiction is actually a fixation on avoiding the individual's cognitive, emotional, and social experiences, especially the craving for alcohol and negative emotions. The key to break the vicious cycle of addiction is to make clients accept their negative emotions and internal pain and reduce their experiential avoidance. Mindfulness, which emphasizes openness and acceptance, that can help patients with alcohol use disorder accept their negative emotional experience and drinking craving, thus improving the curative effect (28). In a systematic review of studies on the efficacy of VRET for substance dependence, only five studies were selected for review which investigated VRET efficacy for the treatment of alcohol craving (one study) and nicotine craving and dependence (four studies). The review reported that VRET was effective in reducing nicotine craving and facilitating smoking cessation. In addition, the review also indicated that VRET was more effective than cognitive behavioral therapy to alleviate alcohol craving, but the selected study was limited by small sample size and short period of follow-up (29).

### 1.5. Rationale of the study

Since alcohol craving is a major factor leading to disease relapse in patients with alcohol use disorder (5, 7), it is essential to focus on the monitoring and intervention of craving to improve efficacy. However, the following problems exist in clinical practice: first, there is a lack of objective methods to detect psychological dependence on alcohol in clinic, and alcohol craving can only be quantified subjectively through psychological rating scales. Second, the treatment of alcohol use disorder, especially the effective intervention aimed at treating psychological craving, is lacking, and patients are prone to relapse.

Hence, it is important to explore an objective detection method for alcohol craving. Medical detection technology based on electroencephalogram (EEG) can reflect neuropsychological factors from different perspectives and can also quantify brain energy fluctuations under specific psychological activities to a certain extent (8). Monitoring event-related potential (ERP) of alcohol craving evoked by alcohol cues, which are a type of task-state EEG, may be helpful for objectively evaluating the psychological activities associated with craving.

In view of the current difficulties in treating alcohol use disorder (5, 7, 30, 31), it is of great significance to investigate the effects of new treatment methods or adjuvant therapy. Acceptance and commitment therapy (ACT) facilitates the development and maintenance of health behavioral improvements (20). With the promising potential of ACT in the treatment of affective disorders and substance use disorders (SUDs), it may be promising to treat alcohol use disorder. In addition, virtual reality exposure therapy (VRET), an innovative therapy technique utilizing computer virtual reality technology that treats mental disorders well, is also worthy of evaluating its efficacy for use in the treatment of alcohol use disorder.

### 1.6. Objectives

#### 1.6.1. Primary objectives

The primary objective was to evaluate the efficacy of virtual reality exposure therapy (VRET) to ameliorate alcohol craving as compared with acceptance and commitment therapy (ACT) and treatment as usual across four timelines, such as t_0_ (pre-intervention), t_1_ = 4 weeks (immediately after the end of intervention), t_2_ = 12 weeks (8 weeks after the end of intervention), and t_3_ = 24 weeks (20 weeks after the end of intervention).

#### 1.6.2. Secondary objectives

The secondary objectives were as follows:

To evaluate the efficacy of virtual reality exposure therapy (VRET) to ameliorate the severity of alcohol use disorder as compared with acceptance and commitment therapy (ACT) and treatment as usual across four timelines, such as t_0_ (pre-intervention), t_1_ = 4 weeks (immediately after the end of intervention), t_2_ = 12 weeks (8 weeks after the end of intervention), and t_3_ = 24 weeks (20 weeks after the end of intervention).To assess the efficacy of virtual reality exposure therapy (VRET) to ameliorate comorbid depression and anxiety symptoms as compared with acceptance and commitment therapy (ACT) and treatment as usual across four timelines, such as t_0_ (pre-intervention), t_1_ = 4 weeks (immediately after the end of intervention), t_2_ = 12 weeks (8 weeks after the end of intervention), and t_3_ = 24 weeks (20 weeks after the end of intervention).To assess the efficacy of virtual reality exposure therapy (VRET) to normalize event-related potential (ERP) in electroencephalogram (EEG) as compared with acceptance and commitment therapy (ACT) and treatment as usual across four timelines, such as t_0_ (pre-intervention), t_1_ = 4 weeks (immediately after the end of intervention), t_2_ = 12 weeks (8 weeks after the end of intervention), and t_3_ = 24 weeks (20 weeks after the end of intervention).

## 2. Methods and analysis

### 2.1. Study design and setting

This multicenter, three-armed, parallel, single-blind randomized controlled trial is expected to run for a duration of 3 years (from May 2023 to April 2026). The proposed study site for subject recruitment is the Second Affiliated Hospital of Xinxiang Medical University, Henan, China, and Advanced Medical and Dental Institute, Universiti Sains Malaysia.

### 2.2. Sample size

The estimated sample size will be calculated using the G^*^Power 3.1.9.7 sample size calculator, using the sample size calculation for repeated measure ANOVA and within–between interaction, whereby the type I error was 0.05, the power was 0.8, the number of groups was three (VRET, ACT, and TAU groups), the number of measures was five (degree of alcohol craving, severity of alcohol use disorder, depression symptoms, anxiety symptoms, and changes in ERP), and the effect size was 0.13, which was cited from a randomized clinical trial that compared the efficacy of virtual reality therapy with multisensory stimulation and cognitive behavioral therapy in alleviating alcohol craving in alcohol dependence patients (32). The estimated total sample size needed was 120 (after inclusion of 30% dropout), in which 40 subjects per group are required.

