### 2.9. Measures

This study follows the Standard Protocol Items: Recommendations for Intervention Trials (SPIRIT) 2013. The checklist for SPIRIT is included in Appendix 3. The schedule for assessments in this study is summarized in Table 1. There will be four timelines of assessment. Baseline assessment (t_0_) commences after the randomization of participants into the three intervention groups (VRET, ACT, and control groups), wherein the sociodemographic, clinical, and alcohol use characteristic questionnaire, Alcohol Use Disorder Identification Test (AUDIT), Penn Alcohol Craving Scale (PACS), Hamilton Anxiety Rating Scale (HAM-A), and Hamilton Depression Rating Scale (HAM-D) are administered, while event-related potential (ERP) detection in electroencephalogram (EEG) is performed in the participants. Then, during follow-up assessment, such as t_1_ = 4 weeks (immediately after completion of intervention), t_2_ = 12 weeks (8 weeks after completion of intervention), and t_3_ = 24 weeks (20 weeks after completion of intervention), the questionnaires are re-administered to the participants which include alcohol use characteristics, AUDIT, PACS, HAM-D, and HAM-A, while ERP detection in EEG is re-assessed. The serial assessments will be carried out by a research assistant who is not involved in the research project and does not know about the objectives of the study. The research assistant will receive some training on the administration of the measures before the data collection begins. To ensure that the participants complete the serial assessments and interventions, an appointment card is given to each participant with the next appointment date written on the card. Emails and messages will be distributed 3 days prior to the appointment to remind the participants regarding the appointment date, and if any participant does not reply, a phone call will be made a day before the appointment date.

**Table 1 T1:** Schedule of assessments of the study outcome measures.

	**Enrollment**	**Allocation**	**Post-allocation**		
**Time**	* **–t** _1_ *	***t**_0_* **(0 week)**	* **t** _1_ * **(4 weeks)**	***t**_2_* **(12 weeks)**	* **t** _3_ * **(24 weeks)**

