### 2.10. Data analysis

Data analysis will be carried out using the Statistical Package for Social Sciences version 26 (SPSS-26, Inc., Chicago, IL, USA). Descriptive statistics for sociodemographic, clinical, and alcohol use characteristics, AUDIT, PACS, HAM-D, and HAM-A scores, and ERP will be computed. For nominal and ordinal data, these will be presented in frequency and percentage. For continuous data, it will be presented as mean and standard deviation if the variable is normally distributed. While for non-normally distributed data, it will be presented as median and interquartile range. The normality of the data will be determined by Shapiro–Wilk test.

As for the assessment of the primary outcome, one-way ANOVA with false discovery rate adjustment is used to compare the mean of the outcomes (PACS, average number of drinks during drinking days, frequency of binge drinking in the previous week, and the number of hazardous drinks per day or per week) between the three groups (VRET, ACT, and control groups) at each specific time point (t_0_, t_1_, t_2_, and t_3_). While for the main analysis, mixed ANOVA is used to evaluate the interaction of intervention and time on the outcomes will be computed (outcomes: PACS, average number of drinks during drinking days, frequency of binge drinking in the previous week, and the number of hazardous drinks per day or per week; interaction: intervention × time; whereby time is the within-subject factor, while intervention is the between-subject factor). The main effect of the interaction will be presented as estimated marginal mean and standard error of mean. The primary outcome assessment will follow the intent-to-treat principle. The data analysis for the secondary outcomes (AUDIT, HAM-D, and HAM-A scores and ERP) will be analyzed in the same way as the primary outcomes. Statistical significance is set at *p* < 0.05 and is two-tailed.

As for the management of missing data, if there is only 5% of missing data or less, it will be ignored and data analysis will proceed. However, if the missing data are from 5 to 40% and are missing randomly, multiple imputations with restricted maximum likelihood estimates will be performed using Stata 15, to estimate the missing values. However, if the missing data are more than 40% or are completely randomly missing or non-randomly missing, data analysis of the remaining data will proceed, and the missing data issue will be reported under the limitation of the study (46).

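### The sample size calculation counts five outcome scales as repeated measures where the planned test has four time points, so the stated 80% power at 120 patients is not supported

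*Protocol article*

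**What the plan says.** Section 2.2 (Sample size) describes a G*Power calculation "using the sample size calculation for repeated measure ANOVA and within–between interaction". Its inputs are: "the type I error was 0.05"; "the power was 0.8"; "the number of groups was three (VRET, ACT, and TAU groups"); an effect size of 0.13; and "the number of measures was five (degree of alcohol craving, severity of alcohol use disorder, depression symptoms, anxiety symptoms, and changes in ERP"). The result is: "The estimated total sample size needed was 120 (after inclusion of 30% dropout), in which 40 subjects per group are required".

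Section 2.9 (Measures) states: "There will be four timelines of assessment". These are t0, t1 (4 weeks), t2 (12 weeks) and t3 (24 weeks), and Table 1 schedules every outcome at all four. Section 2.10 (Data analysis) makes a mixed ANOVA the main analysis, run for each outcome, with time as the within-subject factor and intervention as the between-subject factor.

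Section 2.2 does not give the correlation among repeated measures, the nonsphericity correction, the sample size before dropout, or the formula used to allow for dropout.

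**The concern.** The number of measures in this procedure is the number of levels of the within-subject factor. In this trial that factor is time, with four levels. Craving, disorder severity, depression, anxiety and ERP are five separate outcomes, each analysed in its own model, and never levels of one factor. Section 2.2 therefore sizes a test that the trial will not run.

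The error is in the favourable direction. Other inputs being equal, more measures raise the noncentrality and lower the sample size required. Section 2.2 is the article's only justification of trial size. If its 80% is overstated, a null intervention-by-time result on craving would be read as coming from a better-powered trial than it was.

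**Working it through.** **Inputs from the documents.** Groups k = 3, alpha = 0.05, target power 0.80, effect size 0.13 (taken as Cohen's f, the scale this procedure uses), 1:1:1 allocation, 30% dropout. Number of measures m = 5 as written in section 2.2, and m = 4 from sections 2.9 and 2.10.

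**Assumptions, because not stated.** Correlation rho = 0.5 and epsilon = 1 (the G*Power defaults) to start with; rho is varied below.

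**Formula.** Noncentral F with λ = f² × N × m × epsilon / (1 − rho), df1 = (k − 1)(m − 1) × epsilon, df2 = (N − k)(m − 1) × epsilon.

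**Step 1: reproduce the plan's 120 with m = 5.**

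- At rho = 0.5, the smallest N is 91 (power 0.801), or 93 for equal groups. For N = 93: λ = 0.0169 × 93 × 5 / 0.5 = 15.72, df 8 and 360, power 0.811.
- 93 × 1.3 = 120.9, which is close to 120. 93 / 0.7 = 132.9, which is not.
- A second route exists. At rho of about 0.54 to 0.55, the equal-group N is 84 (power 0.801 to 0.812), and 84 / 0.7 = 120 exactly.

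So 120 follows from m = 5 either with rho 0.5 and multiplication by 1.3, or with rho about 0.54 to 0.55 and division by 0.7. The text does not show which was used.

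**Step 2: the same calculation with m = 4.** At rho = 0.5, the smallest N is 103 (power 0.800), or 105 for equal groups (power 0.810). 105 / 0.7 = 150. The change in m alone moves the evaluable N from 93 to 105.

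**Step 3: power of the planned design.** 120 × 0.7 = 84 completers. At m = 4 and rho = 0.5: λ = 0.0169 × 84 × 4 / 0.5 = 11.36, df 6 and 243, power 0.697. Over the unstated correlation, with f = 0.13 and epsilon = 1:

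| rho | Power, 84 completers, m = 4 | Power, 84 completers, m = 5 |
|---|---|---|
| 0.3 | 0.525 | 0.583 |
| 0.4 | 0.602 | 0.664 |
| 0.5 | 0.697 | 0.760 |
| 0.54 | 0.739 | 0.801 |
| 0.55 | 0.750 | 0.812 |
| 0.6 | 0.807 | 0.864 |
| 0.7 | 0.918 | 0.953 |

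The two reconstructions of 120 are the rows at rho 0.5 and at 0.54 to 0.55. They give 0.70 and 0.74 to 0.75 at m = 4.

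**Step 4: other reference values at m = 4 and rho = 0.5.** With all 120 evaluable, power is 0.868. With 84 completers and epsilon 0.75, it is 0.60. The effect detectable with 80% power on 84 completers (epsilon 1) is f = 0.144.

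**The case against.** A reader might infer three stronger points. The documents do not support them.

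- **That dropout was wrongly added by multiplying by 1.3.** The article gives neither a formula nor a pre-dropout N. Multiplication by 1.3 fits at the default correlation, though it gives 120.9 and not exactly 120. Correct division by 0.7 gives exactly 120 if rho was about 0.54 to 0.55. The ×1.3 step is an inference from the reproduction. If the inflation was done correctly, the wrong number of measures alone costs about five to six points of power (0.74 to 0.75 against 0.80).
- **That 120 patients cannot give 80% power.** They can under some values of the unstated inputs: 84 completers give 0.81 at rho 0.6 and 0.92 at rho 0.7, and 120 evaluable patients give 0.87 at rho 0.5. The high-correlation route does not rescue section 2.2 as written, however. At rho 0.6 its five measures would need only 75 evaluable patients (98 by multiplication, 108 by division), not 120.
- **That 150 patients must be enrolled.** That figure rests on the assumed rho of 0.5. The claim can be corrected at the present size.

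It can also be said that 84 completers understates the information available. Section 2.10 specifies intent-to-treat for the primary outcome and multiple imputation for 5 to 40% of data missing at random, so patients lost late may contribute. This softens the shortfall but does not remove it. Imputation does not restore complete data, and section 4 says that data from participants who withdraw will be discarded.

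None of these objections touches the input error, which needs no assumption to see.

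**Conclusion.** Section 2.2 is wrong as written: it enters five outcomes where the planned analysis has four repeated measurements, and the 80% power stated for 120 patients is not supported. At the correlations that reproduce the plan's own 120, with f = 0.13 and epsilon 1, power after the planned 30% dropout is about 0.70 to 0.75. The risk of missing the target effect is then 25 to 30%, where the plan implies 20%.

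The shortfall depends on the full 30% loss and on a correlation below about 0.6. It is larger at lower correlations or under nonsphericity, and absent at higher correlations or with little dropout. Confidence is high on the five-versus-four error and lower on how dropout was handled.

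**What to change.** In section 2.2:

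- Set the number of measurements to four (t0 to t3).
- State the assumed correlation and epsilon, using the sponsor's own values with a reason for them.
- Give the evaluable N and the dropout formula (evaluable N divided by 0.70).
- Restate the power for 120 enrolled and 84 completers. If rho = 0.5 and epsilon = 1, that is about 70% at f = 0.13, or 80% at f of about 0.144.

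This is a change of wording only. It needs no extra enrolment and no change in procedures. The cost is a less favourable stated power.
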